### Outcome measures

Figure 1 depicts the timing and frequency of all study measures. Blood analyses, blood pressure, anthropometric measurements and 7-day food records are taken at baseline and every 3 months afterwards until end of study (up to 33 months). Complete blood analyses are done at baseline, 1 year and end of study while blood analysis pertinent to the treatment are done every three months (Table 5). The primary outcome is the percentage of patients alive at end of study without BC recurrence (disease in the same or opposite breast or any metastasis). The primary outcome is assessed at each collaborating centre by the collaborating oncologist and confirmed by hospital pathological results which are communicated to the coordinating centre. Secondary end points include glycemic control including blood glucose and glycated hemoglobin (HbA1c), cardiometabolic variables including body weight, waist circumference, body mass index (BMI), blood pressure, C-reactive protein (CRP) and blood lipids, hormonal measures including insulin, insulin-like growth factor-1 (IGF-1), estradiol, testosterone and sex hormone binding globulin (SHBG), and epigenetic markers (microRNA). Program adherence and any difficulty noticed, medications and medication changes, as well as any unusual or adverse events, including illness or stressful issues, that occurred since the last clinic visit are recorded in detail.

**Table 5 Tab5:** Blood analyses performed during the study

Parameters	Baseline, 12 mo and study end	Every 3 months
25(OH)D	x	x
Calcium	x	x
Glucose	x	x
HbA1c	x	x
Insulin	x	
Triglycerides	x	
Total Cholesterol	x	
LDL-C	x	
HDL-C	x	
AST/ALT	x	
CRP	x	
Estradiol	x	
Testosterone	x	
SHBG	x	
IGF-1	x	
microRNA	x	
For future analyses	x	x

*AST/ALT*: aspartate transaminase/alanine transaminase, *CRP*: C-reactive protein, *HbA1c*: hemoglobin A1c, *HDL-C*: high density lipoprotein cholesterol, *IGF-1*: insulin-like growth factor-1, *LDL-C*: low density lipoprotein cholesterol, *SHBG*: sex hormone binding globulin, *25(OH)D*: 25-hydroxyvitamin D.

Blood samples and all information regarding the patient are sent to the coordinating centre where blood samples are centrally analyzed and information entered electronically and statistically analyzed for the interim and end of study reports.

### Biochemical analyses

Serum vitamin D and IGF-1 are analyzed using DiaSorin kits on Liaison XL analyzer (DiaSorin) by chemiluminescent method (CLIA). The HbA1c value is analyzed using whole blood collected in EDTA Vacutainer tubes (Vacutainer; Becton, Dickinson and Co) by a turbidimetric inhibition latex immunoassay (TINA QUANT Roche Diagnostics) on Cobas C6000 analyzer (Roche). Serum glucose, total cholesterol, triglycerides, high-density lipoprotein cholesterol (HDL-C), low-density lipoprotein cholesterol (LDL-C), are measured using reagents and analyzer (Cobas C6000) by Roche Diagnostics according to the manufacturer’s instructions. Serum insulin, estradiol, testosterone and SHBG are performed on the same analyzer by electro-chemiluminescent method (ECLIA). Nephelometric quantification of CRP is performed on BNP ProSpec nephelometer (Siemens Healthcare Diagnostics) according to the manufacturer’s instructions. Serum samples are obtained by blood collected in Vacutainer tubes without anticoagulant (Becton, Dickinson and Co) and analyzed within 24 hours. All analytes are measured in the coordinating hospital routine analytical laboratory undergoing quality control procedures.

### MicroRNA Analysis

Previous studies have demonstrated that microRNAs (miRNAs) are frequently dysregulated in human cancers, including BC [50, 51] and may be modified by the glycemic load of the diet [41]. Computational models are important for the understanding of biological systems [52]. The following are the procedures to identify and analyze miRNA. These analyses will be conducted at the Laboratory of the Biomedical Sciences Department at the University of Catania (Italy).

#### Identification of plasma miRNA in BC

Plasma samples are randomly selected for the analysis by the Human Serum & Plasma miScript miRNA PCR Array (Qiagen) that profiles the expression of 84 miRNAs. In this phase, miRNA expression patterns are analyzed in BC patients according to the lifestyle and dietary intake.

#### Circulating microRNA analysis

miRNAs can be easily purified from a number of patient body fluids. Several studies shown that miRNAs were present in serum and plasma and easily detectable by a sample of peripheral blood. Circulating miRNAs may be important players in the formation of the tumor microenvironment and metastatic evolution by promoting epithelial to mesenchymal transition (EMT) of tumor cells. RNA and miRNAs fraction are extracted from 200 μL of plasma are isolated by miRNeasy Serum/Plasma Kit (Qiagen, Hilden, Germany) according to the manufacturer’s recommendations Extracted miRNAs are reverse transcribed into cDNA and analyzed by miScript SYBR Green PCR Kit (Qiagen).

#### Validation of circulating miRNAs in BC tissues

Data obtained in the previous two steps above are validated in tumor tissue samples to confirm the origin source of the circulating miRNA previously identified.

#### miRNAs and epithelial mesenchymal transition (EMT)

miRNAs, a class of small non-coding RNA molecules that post-transcriptionally regulate gene expression, are attractive candidates for regulating stem cell self-renewal, cell fate decisions and cell plasticity. For this reason, miRNAs analysis is carried out to shed light on the post-transcriptional control of EMT and stemness.

#### Analysis of EMT genes

Publicly available gene expression datasets are analyzed to identify pathways involved in EMT. For this reason a comparative analysis of expression of master regulators of EMT genes (Beta-Catenin, OPN, Twist1/2, Snail1/2, Zeb1/2, N-cad, Vim, E-cad and NGAL) will be performed. GSEA (Gene Set Enrichment Analysis http://broad.mit.edu/gsea) will assess whether the potential pathways involved in EMT, identified in the previous analysis, will be confirmed using a different computational approach. The key genes, representing the highly connected hubs in the identified networks, are assessed by qRT-PCR and IHC on selected archival tumor series to determine their diagnostic and prognostic value according to clinical information, lifestyle and dietary intake.

#### MiRNAs and their role in modulating EMT

Validated miRNAs are analyzed by in silico approaches (miRanda, miRbase, TargetScan) to evaluate if EMT genes previously analyzed are included among their putative target genes. miRNAs here identified and their putative target genes are analyzed in BC tumor tissue, positive for canonical mesenchymal markers, such as Vimentin and N-cadherin. Evaluation of EMT markers are carried out by IHC followed by laser micro-dissection. Further functional experiments are performed to validate in silico considerations.

#### Risk recurrence in BC by computational modeling

The development of a computational model based on agent based modelling, differential equations or Petri nets could lead to a validated tool able to predict the efficacy of the dietary regimen. The model is fit with data coming from the diet regiment components, diet effects, life style, and from plasma miRNAs analysis. miRNAs expression allows the model to be tuned to find evidences that may be relevant to predict the time and the probability of recurrence risk.

### Sample size

Considering a 20% recurrence rate within 3 years in most collaborating centres for BC cases specified in Table 2, and a predicted rate of 10% in the high intensity arm, with power of 80% and two-sided alpha of 0.05, the number of subjects are 506 (*n* = 253 in each arm).

### Statistical analyses

All randomized patients will be analysed considering the “intention-to-treat” principle (ITT analysis). Results will be expressed as percentages or means ± SEM or 95% confidence intervals (CI).

#### Primary analyses

The primary analyses will assess the between-treatment difference in BC recurrence measured as disease-free survival (DFS), calculated as the percentage of patients alive without recurrence of disease at study end (up to 33 months from randomization). BC recurrence is defined as the relapse of the disease or metastasis either in the same breast (including new positive lymph nodes), or the opposite breast or in distant organs. The duration of DFS in patients lost at follow-up will be censured at the date of the last day the patient was considered free of disease. Between-treatment differences in DFS will be analyzed by *log-rank* test. Kaplan-Meier curves will be provided to estimate median DFS and 95% CI. To address the impact of potential imbalance in prognostic factors we will repeat the primary analysis using the *log-rank* test stratified by stage, age, family history of BC, time since diagnosis, molecular subtype, medication use, smoking, baseline waist circumference and dietary variables (baseline GI, dietary fiber, saturated fat, vegetables/fruit, meat, sweets/desserts). Missing data for covariates will be handled by using the missing indicator method.

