### Recruitment and randomization

Eligible participants are recruited in five oncologic centres in Italy (four in Southern Italy and one in Northern Italy). Details of the recruiting centres can be found in Table 3. Eligible participants are contacted either by phone or during one of their follow-up visits and offered to hear more about the study during an information session (either group session or a one-to-one session to accommodate all needs). Eligible participants are explained the study details and are given an informed consent document to take home which they bring back at the baseline visit. At the baseline visit, after obtaining written consent the participant is sent for a blood test and other measurements, is randomized to one of the two arms of the study, receives the advice on the program according to her randomization arm and is given the next appointment slip. Participants are contacted by phone monthly for the first three months and once between visits afterwards. Study visits are scheduled every 3 months until end of study (33 months).

Randomization is done electronically in real time for all recruiting centres and is stratified by stage (I/IIA vs. IIB/IIIA) and age (<50 yrs or ≥50 yrs) at diagnosis and is based on a permuted block design with block size of 4. Stratification by stage and age is done because we expect these variables to affect the outcomes. To prevent any possible study bias the randomization sequence will be done off-site by a third party statistician (Contract Research Organization, Naples, Italy) who will not have contacts with the study participants. The PI is blinded to the randomization of the study participants but not the staff involved in the clinic visits.

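### The primary log-rank test leaves out the stage and age strata used in randomisation: valid, but mildly conservative, and improvable at almost no cost

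*Protocol article*

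**What the plan says.** Under Recruitment and randomization, allocation is "stratified by stage (I/IIA vs. IIB/IIIA) and age (<50 yrs or ≥50 yrs) at diagnosis and is based on a permuted block design" with blocks of 4. The reason given is: "Stratification by stage and age is done because we expect these variables to affect the outcomes".

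Under Primary analyses, the decision test carries no strata: "Between-treatment differences in DFS will be analyzed by" a log-rank test. Stratification appears only afterwards, as a check on chance imbalance: "we will repeat the primary analysis using the *log-rank* test stratified by stage, age, family history of BC, time since diagnosis, molecular subtype", followed by medication use, smoking, baseline waist circumference and six baseline dietary variables. That makes 14 factors in all. Because this repeat is set against the primary analysis, the primary test has to be read as unstratified. It is a stated choice and not a detail left for a later plan.

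No analysis stratified by the two randomisation factors alone is described.

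**The concern.** Blocking within prognostic strata keeps the arms balanced on stage and age, so the log-rank statistic varies less from trial to trial than it would under simple randomisation. The plain log-rank variance does not know this. It still counts the between-stratum variation that the blocking removed. The test therefore rejects less often than its nominal 5% under the null and gives up some power under the alternative.

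The premise that the strata are prognostic is the protocol's own. The design rates imply only about 76 events, so information that the design has already secured is worth using. The planned repeat does not recover it, because it adds 12 factors to the two that matter here.

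**Working it through.** **Inputs from the protocol (Sample size).** Control arm: "Considering a 20% recurrence rate within 3 years in most collaborating centres for BC cases specified in Table 2". Test arm: "a predicted rate of 10% in the high intensity arm". Power 80%, two-sided alpha 0.05, 253 per arm, follow-up up to 33 months.

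**Inputs not in the protocol, assumed here.** Stage hazard ratio (HR) 1 to 6; age HR 1 to 2; 40% of women in the higher-risk level of each factor, the two factors independent; exponential disease-free survival.

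**1. The plan's own figure.** For two proportions, n per arm = [1.96·√(2·0.15·0.85) + 0.8416·√(0.2·0.8 + 0.1·0.9)]² / 0.1² = (0.990 + 0.421)² / 0.01 ≈ 199, or 398 in total (438 with continuity correction). The stated 506 is not reproduced from the stated inputs; it would need an unstated allowance for loss of about 20%. That is a separate matter, and 506 is taken as given below.

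**2. Design effect and events.** Exponential HR = ln 0.9 / ln 0.8 = 0.472. Expected events = 253 × 0.20 + 253 × 0.10 = 75.9.

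**3. Size and power.** Simulated trials of 506 women, permuted blocks of 4 within four stage-by-age strata, 36 months, no loss. There were 20,000 null runs (SE about 0.15 points) and 10,000 alternative runs (SE about 0.3 points) per row. Within each row the treatment effect is set so that the overall rates are 20% and 10%.

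| Stage HR / age HR (assumed) | Size, plain | Size, stratified | Power, plain | Power, stratified | Gain, points |
|---|---|---|---|---|---|
| 1 / 1 | 4.99% | 4.97% | 89.20% | 89.23% | 0.03 |
| 1.5 / 1.2 | 4.85% | 4.95% | 88.92% | 89.09% | 0.17 |
| 2 / 1.5 | 4.81% | 5.10% | 89.63% | 90.19% | 0.56 |
| 3 / 1.5 | 4.33% | 5.09% | 89.85% | 90.91% | 1.06 |
| 4 / 2 | 3.63% | 4.86% | 90.46% | 92.04% | 1.58 |
| 6 / 2 | 3.19% | 5.00% | 90.50% | 92.86% | 2.36 |

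With no prognostic effect nothing is lost. The stratified test stays near 5% throughout.

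**4. Shorter follow-up with loss.** With 33 months and an assumed 20% loss (about 63 events), power goes from 83.1% to 83.4% (stage/age HR 1.5/1.2), 82.7% to 83.1% (2/1.5) and 83.5% to 84.5% (3/1.5).

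**5. A weaker treatment effect.** With a treatment HR of 0.55, which the protocol does not state, and strata prevalences of 45% and 35% (8,000 runs, 33 months), power goes from 71.3% to 72.2% (2/1.5), 69.7% to 71.4% (3/1.5) and 69.5% to 73.0% (4/2). A second simulation of the same three settings gave gains of 0.8, 1.7 and 3.3 points.

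**6. The planned repeat.** If all 14 factors are crossed and each is only binary, there are 2¹⁴ = 16,384 strata for 506 women. In 600 simulated trials about 1 of 76 events' worth of information remained and power was about 1%. Even with only six extra binary factors (4 × 2⁶ = 256 strata), about 40 events' worth remained and power was 62%. If the list is instead read as one factor at a time, stage and age are still never used together.

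**The case against.** The strongest reply is that the plain log-rank is a valid test and its error runs in the safe direction. That stands. A reader might infer that the primary test is miscalibrated in a way that puts the conclusion in doubt. It does not: type I error is never inflated in any setting tried, and a significant result would hold. The plain test also exceeded 80% power at the design effect in every setting above, including 33 months with an assumed 20% loss.

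A reader might also take the loss to be about 3 power points. The documents do not support that as the general figure. It needs both the strongest strata effects (4/2) and a treatment HR of 0.55, whereas the protocol's own rates imply about 0.47.

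A further tempting inference is that the reported HR would be pulled towards 1. The Primary analyses section plans a log-rank test and Kaplan-Meier curves and names no treatment HR, so this is hypothetical. It would also be small. For a within-stratum HR of 0.472, the large-sample unstratified value is 0.477, 0.481 and 0.488 at stage/age HR 2/1.5, 3/1.5 and 4/2. The largest shift on the log scale is ln(0.488/0.472) ≈ 0.033, against a standard error of roughly 2/√76 ≈ 0.23. It is a difference between a marginal and a conditional quantity rather than a bias.

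Finally, a stratified repeat is already planned. That does not answer the point, because under neither reading does the repeat use the two randomisation factors together and alone.

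**Conclusion.** The point holds as a minor one. The primary test ignores the two factors on which randomisation is blocked, and no usable analysis in the protocol makes this good. For stage HR 1.5 to 4 and age HR 1.2 to 2, the plain test's true size is about 4.9% down to 3.6%. The power lost is about 0 to 2 points at 20% versus 10%, and up to about 3 points at a treatment HR of 0.55.

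The direction follows from the protocol's own statement that stage and age affect outcome. The size rests on assumed strata effects and prevalences, none of which the protocol gives; if the strata are barely prognostic, the loss is nil.

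**What to change.** Make the primary test the log-rank stratified by the randomisation factors: stage group as used in randomisation, and age <50 or ≥50. First state which stage stratum holds the stage IIIC women whom Table 2 admits, because the randomisation strata stop at IIIA. Give any treatment HR from a Cox model with the same strata. Keep the unstratified log-rank as a supportive analysis.

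The cost is one sentence in Primary analyses plus the IIIC clarification. Four strata with about 76 events lose under about 1% of the information (ratio to the unstratified test 0.993 in simulation). Recruitment has started, so the change should be recorded before any comparison of outcomes by arm, including the interim analysis.

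### The adjusted repeat of the primary analysis, a log-rank test stratified by 14 factors, loses most of its information in 506 patients with about 76 expected events

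*Protocol article*

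**What the plan says.** Under Primary analyses, the protocol article compares disease-free survival (DFS) between arms with an unstratified log-rank test. To address possible imbalance in prognostic factors it then repeats that analysis as a log-rank "test stratified by stage, age, family history of BC, time since diagnosis, molecular subtype, medication use, smoking, baseline waist circumference and dietary variables". A parenthesis names six dietary variables: glycaemic index, fibre, saturated fat, fruit and vegetables, meat, and sweets or desserts. With the eight factors before them, the list has 14.

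The same section adds: "Missing data for covariates will be handled by using the missing indicator method".

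Under Sample size the plan assumes a "20% recurrence rate within 3 years in most collaborating centres" and "a predicted rate of 10% in the high intensity arm", "with power of 80% and two-sided alpha of 0.05", and states that "the number of subjects are 506", 253 per arm. DFS is assessed "at study end (up to 33 months from randomization").

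Two other places bear on the point. Recruitment and randomization stratifies allocation by stage and age only, two levels each. Secondary analyses mentions Cox and logistic models, but for how each variable relates to prognosis, not for an adjusted comparison of the arms.

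**The concern.** A stratified log-rank test compares the arms only within strata. It suits a few coarse factors. Each added factor at least doubles the number of possible cells, and an event in a cell with no patient of the other arm at risk contributes nothing.

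At stake is the reading of the trial's result. The repeat is there to show whether the primary finding survives allowance for prognosis. If it loses most of its events, it will often be non-significant for want of information, and that could be taken to mean that the effect disappears on adjustment. If the primary result were itself distorted by chance imbalance, the repeat would have little ability to show it. The test also yields no adjusted hazard ratio that would let a reader separate loss of precision from a change in the estimate.

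**Working it through.** **Inputs from the protocol article.** 506 patients, 253 per arm; 20% versus 10% recurrence within 3 years; two-sided alpha 0.05; 14 factors (8 + 6); randomisation strata 2 × 2 = 4.

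**The plan's own figure.** The stated inputs do not return 506. The usual two-proportion formula gives 199 per arm (398 in total), or 219 per arm (438) with continuity correction. Reaching 253 would need an unstated loss allowance of 1 − 199/253 = 21% or 1 − 219/253 = 13%. That is a separate matter; here 506 is used only as the number of patients. Power for 20% versus 10% at 253 per arm is 88.5%.

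**Expected events.** 253 × 0.20 + 253 × 0.10 = 75.9, about 76. The rates are for 3 years. Scaled to 33 months with constant hazards, the count is 253 × [(1 − 0.8^(33/36)) + (1 − 0.9^(33/36))] = 253 × (0.185 + 0.092) = about 70. The figures below use 36 months, which favours the plan slightly.

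**Cells.** At the minimum of two levels per factor, 2^14 = 16,384 cells, or 506/16,384 = 0.03 patients per cell. With even, independent splits, the chance that a patient is alone is (1 − 1/16,384)^505 = 0.97, which is about 490 of 506 patients.

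**What an event contributes.** For an event in a stratum with n patients at risk, n1 of them in one arm, the variance term is n1(n − n1)/n². It is zero, as is the observed-minus-expected term, when n1 = 0 or n1 = n.

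**Simulation.** 400 trials per row, exponential times giving 20% and 10% at 36 months, no dropout, no missing covariates, and factors unrelated to outcome, so that only sparsity is measured. The article gives neither categories nor correlations, so splits and correlations (r, on the latent scale) are assumptions shown as a range. Information is the mean summed variance divided by the unstratified 18.99.

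| Strata | Patients alone | Informative events (of about 76) | Information kept | Power |
|---|---|---|---|---|
| None | 0% | 76 | 100% | 88% |
| Stage and age only (4 cells) | 0% | all | 100% | 88% |
| 14 factors, 50/50, r = 0 | 97% | 1.1 | 1.4% | 0.2% |
| 14 factors, 50/50, r = 0.2 | 91% | 3.9 | 4.8% | 6.5% |
| 14 factors, 50/50, r = 0.3 | 84% | 8 | 10% | 17% |
| 14 factors, 50/50, r = 0.5 | 68% | 19 | 24% | 36% |
| 8 clinical 80/20, 6 dietary 50/50, r = 0 | 76% | 10 | 13% | 22% |
| Same, r = 0.3 | 62% | 22 | 26% | 34% |
| 14 factors, 80/20, r = 0 | 52% | 27 | 32% | 43% |
| 14 factors, 80/20, r = 0.3 | 48% | 34 | 43% | 57% |
| Four subtypes, three smoking levels, dietary thirds, r = 0.2 | 99% | 0.5 | 0.6% | 0% |

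Simulation error on a power near 50% is about √(0.25/400) = 2.5 percentage points. Repeat runs of the first two-level case and of the most favourable case agreed within that error.

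Stratifying by the two randomisation factors costs nothing, so the loss comes from the length of the list. Dropping the dietary variables alone is not enough: the eight clinical factors, split evenly and independent, keep only about 55% of the information.

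**The case against.** The strongest reply is that this is a supportive analysis. The primary comparison is the unstratified log-rank test, and no sample size or success criterion in the article rests on the repeat. That stands and limits the consequence.

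Second, the trial is not without other protection against imbalance. Stage and age, two of the 14 factors, are stratified at randomisation in blocks of 4. That also stands, so the repeat is the only planned covariate-adjusted treatment comparison, not the only safeguard.

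Third, the size of the loss depends on categories, prevalences and correlations that the article does not give and that a fuller plan may supply. This stands in part. Missing cut-points are no fault in a condensed article, and the missing-indicator rule adds a level only where data are missing. But every two-level setting tried lost more than half of the information, and more levels make it worse.

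Fourth, the article does not say outright that the factors are crossed; they might be taken singly. One test followed by one list reads most naturally as joint, and Sensitivity analyses speaks of a single stratification step. Fourteen one-factor tests would avoid the sparsity but would not adjust jointly for imbalance, which is the stated purpose. The sentence needs rewriting on either reading.

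A reader might go further and infer that the repeat can test nothing because almost every patient is alone in a stratum. The document does not support that in general: it fits even splits with little correlation, or more than two levels, but with skewed or strongly correlated binary factors a weak test remains.

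**Conclusion.** The concern holds as a severe loss of information in the adjusted repeat. With two levels per factor, about half to 97% of patients are alone in a stratum, about 1 to 35 of 76 events inform the test, and power is about 0 to 57% against about 88% unstratified. This rests on joint stratification, on the planned 20% versus 10% effect, and on assumed splits and correlations.

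The repeat would therefore often be non-significant when the planned effect is real, and a null result from it should not be read as evidence of confounding. Nor should a reader conclude that the primary result is compromised: the unstratified test keeps all its events. The weakness does appear to carry into the completer and per-protocol repeats under Sensitivity analyses, which refer to the same stratification step in smaller sets.

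**What to change.** Replace the 14-factor stratified log-rank test with one Cox model for DFS:

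- stratify the model by the two randomisation factors, stage and age;
- adjust for a short, pre-specified list of baseline prognostic covariates, chosen by the sponsor to suit about 76 events;
- keep continuous factors continuous;
- report the adjusted hazard ratio with its 95% CI beside the unstratified log-rank result;
- move the remaining factors, such as the dietary variables, to models labelled exploratory.

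Which covariates to keep is the sponsor's choice, to be fixed before outcome data by arm are examined. The cost is one paragraph of wording and no new data. The downside is a proportional-hazards assumption, which should be checked, and fewer factors in the main adjusted model.
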